### Outcome measures

#### Primary objectives

Primary outcome is assessed using the QuickDash score at 12 months following treatment. The QuickDASH is a patient-reported outcome instrument developed to measure upper extremity disability and symptoms, resulting in a score ranging from no disability (0) to most severe disability (100) [18].

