### Sample size considerations

As indicated above, the primary outcomes are defined as the difference in patient-reported functional outcome as measured by the QuickDASH, measured at 12 months after the injury. The developers of the QuickDASH report that a difference of eight points represents a clinically relevant difference for discriminating between improved and stable patients [22]. A previous observational cohort study by Frima et a.l [23], performed by our research group, found patients who had MIPO surgery had a QuickDASH standard deviation (SD) of 14. Sample size calculations indicate that a study with a power of 80% and two-sided statistical significance level (alpha) of 0.05 would require 2 x 50 participants. Accounting for 20% loss to follow-up and an additional 40% loss after propensity score matching (used to account for confounding, see Statistical Analysis), the total sample size is 220 participants.

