### Statistical analysis

Descriptive results will be presented as mean values with standard deviations and range (SD, range), median values with interquartile range (IQR) or absolute numbers and percentages (%). To control for potential confounding, we will conduct propensity score matching. The propensity score will be estimated using binary logistic regression analysis, with operative or nonoperative treatment as the dependent variable and age, sex, BMI, ASA score, AO classification as covariates in the model. The primary analysis will be performed within the dataset of propensity score matched patients. Normal distribution will be confirmed using the Shapiro–Wilk test. Correlation between continuous variables will be measured using the Pearson correlation coefficient. Missing data will not be imputed. Differences between study groups will be analysed using the independent sample t-test, Mann–Whitney U test, or the Chi-square test. A two-tailed p-value less than 0.05 will be considered significant.

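### The plan pairs a Shapiro–Wilk check with a t-test or Mann–Whitney choice and fixes neither for the primary outcome, so the primary estimand may depend on the data

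*Protocol article*

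**What the plan says.** The primary outcome is QuickDASH at 12 months, a score bounded at 0 and 100 (Primary objectives). Under Sample size considerations the trial is sized on a mean difference: "a difference of eight points represents a clinically relevant difference", the cited earlier cohort "found patients who had MIPO surgery had a QuickDASH standard deviation (SD) of 14", and "a study with a power of 80% and two-sided statistical significance level (alpha) of 0.05 would require 2 x 50 participants".

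The Statistical analysis section places the primary analysis in the propensity-matched patients. It then states: "Normal distribution will be confirmed using the Shapiro–Wilk test". After sentences on correlation and missing data it continues: "Differences between study groups will be analysed using the independent sample t-test, Mann–Whitney U test, or the Chi-square test". It does not say which of these tests applies to the primary outcome, and it names no effect estimate or interval to be set against the 8 points. The protocol gives no mean and no distributional shape for 12-month QuickDASH, and no SD for nonoperatively treated patients.

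**The concern.** A normality check followed by a parametric and a non-parametric alternative is most naturally read as a gate: if Shapiro–Wilk does not reject, use the t-test; if it rejects, use Mann–Whitney. The two branches answer different questions. The t-test goes with a difference in means and a confidence interval that can be compared with 8 points. Mann–Whitney asks whether scores in one group tend to exceed those in the other, and it yields no mean difference. Under the gate, the quantity the trial estimates is settled only once the outcome data are seen, and one of the two possible quantities is not the one that justified the sample size.

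Two things follow. If the Mann–Whitney branch is taken, the primary test itself does not show whether 8 points is ruled in or out. And on a bounded scale with scores near the floor, Mann–Whitney can be significant when the means are equal, if spread and shape differ between the arms.

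**Working it through.** **1. Reproducing the sample size.** Inputs from Sample size considerations: difference 8, SD 14, two-sided alpha 0.05, power 80%. Normal approximation for two means:

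n per arm = 2 × (1.960 + 0.842)² × 14² / 8² = 2 × 7.85 × 196 / 64 = 48.1, rounded up to 49.

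The exact two-sample t-test calculation gives 49.05, so 50 per arm. The stated 2 × 50 is reproduced, which confirms that the trial was sized on a difference in means. Power at 50 per arm is 80.8% (t) or 81.5% (normal approximation).

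**2. How often the gate would lead to Mann–Whitney.** Scores were simulated as scaled beta variables on 0–100 with SD 14 in both arms, 50 per arm, and means 8 points apart. For mean μ and SD σ as fractions of 100, the beta parameters are μk and (1 − μ)k with k = μ(1 − μ)/σ² − 1. The arm means are assumptions. The gate is taken to close if Shapiro–Wilk rejects at 0.05 in at least one arm. Ranges are across repeated runs.

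| Assumed better-arm mean | Trials sent to Mann–Whitney |
|---|---|
| 10–15 | about 100% |
| 20 | 95% |
| 25 | 63–70% |
| 30 | 32–40% |
| 40 | 12–13% |
| 50 | 12% |

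Exactly normal data give about 10%, as two independent tests at 5% should: 1 − 0.95² = 9.75%.

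**3. Equal means, unequal spread.** Same set-up at about 50 per arm, but with equal means and SD 14 in one arm against 20 in the other. The 14 is the protocol's; the 20 is assumed. The rejection rate is that of the full two-stage procedure (pretest, then the selected test).

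| Common mean | Two-stage procedure | t-test |
|---|---|---|
| 15 | 34–37% | about 5% |
| 20 | 18% | about 5% |
| 25 | 11% | about 5% |
| 30 | 9% | about 5% |
| 40 | 6% | about 5% |

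A milder contrast (SD 12 against 16) gives 15% at mean 15 and 10% at mean 20. With equal means and equal SDs of 14 at mean 15, Mann–Whitney rejects in 4.7% of trials and the t-test in 5.1%. With normal data and SD 14 against 20, Mann–Whitney rejects in 5%. Unequal spread alone is therefore not the cause. Near the floor, widening the SD at a fixed mean also changes the skewness and moves the median: at mean 15 the medians are 10.8 (SD 14) and 5.8 (SD 20), and at mean 20 they are 17.1 and 13.3.

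**4. Power for a true 8-point difference, 50 per arm, SD 14.** The t-test has 79–82% at every assumed mean from 6 to 50. Mann–Whitney has 100% at mean 6, 90% at 15, 82% at 25 and 78% at 40. The t-test keeps the stated 80% even when scores are strongly skewed, so no normality pretest is needed to protect it.

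**The case against.** The strongest reply is that the gate is inferred. The protocol says normality will be checked but writes no selection rule, and its list of tests serves all outcomes, including categorical ones such as complications. The check could instead serve the choice between mean with SD and median with IQR, or the Pearson correlation. This stands as far as it goes: the rule is implied, not stated. On the other readings, however, the choice between t-test and Mann–Whitney for the primary outcome is simply left open, which does not remove the problem.

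It can also be said that effect estimates and the matching of tests to outcomes are commonly left to an analysis plan, which is not shown. Silence on those would be no finding. The point here is the procedure the article does state. It is also fair that group means and SDs are to be reported and a mean difference could be computed from them, so the trial would not be wholly unable to address 8 points. That difference would then be descriptive and would not be the primary test.

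Three stronger readings are tempting and not supported:

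- A reader might infer that the primary test will usually be Mann–Whitney. That needs a low 12-month mean, and the protocol gives none.
- A reader might infer that Mann–Whitney rejects whenever only the spread differs. The normal-data result above contradicts this.
- A reader might infer a loss of power. Mann–Whitney power was similar to or higher than the t-test's in the skewed cases.

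**Conclusion.** The point holds in limited form. The sample size rests on a difference in means; the stated analysis leaves the primary test to what is most naturally a data-dependent choice, and one branch does not estimate that difference. This is a defect of estimand and pre-specification, worth correcting before outcomes are analysed, and not one of power.

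Its size depends on assumptions. With SD 14 and 50 per arm, the Mann–Whitney branch would be taken in roughly 63–100% of trials if the better-arm mean is about 25 or lower, and in about 12–40% if it is 30 or higher. The excess rejections under equal means (about 18–37% at means of 15–20, falling to about 6% at 40) further require unequal spread and shape, here SD 14 against 20. The protocol gives no evidence for that contrast and none against it, since its only SD comes from patients who had one type of surgery. These rates illustrate what the procedure can do; they do not predict this trial's result.

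**What to change.** Remove the Shapiro–Wilk test as a gate for the primary outcome. State that the primary analysis is the difference in mean 12-month QuickDASH between operative and nonoperative treatment in the matched set, with a 95% confidence interval, interpreted against 8 points. An unequal-variance t-test, or a linear model with heteroscedasticity-robust or bootstrap standard errors, would serve; the choice among them matters less than fixing one in advance. Keep Mann–Whitney as a sensitivity analysis.

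The cost is about one sentence of wording, with no extra data and no change to the 50 per arm. The downside is that, if scores are strongly skewed, some power is given up relative to Mann–Whitney (for example about 80% against 90% at an assumed better-arm mean of 15), but the stated 80% is kept.

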## Discussion

The LADON study is an international multicenter prospective cohort study with a relatively new methodological study design. The aim of the study is to compare nonoperative and operative treatment of proximal humerus fractures. It is a “natural experiment”, meaning patients receive standard local treatment and surgeons perform standard local procedures. Therefore high participation rates of patients and surgeons are expected. Furthermore, patients are only included after expert panel evaluation when there is proven disagreement between experts, which makes this a unique study design. Through this inclusion process, we create two comparable groups whom received different treatments and where expert disagree about the already initiated treatment. Since we are zooming in on this particular patient group, confounding will be mitigated. In addition, propensity score matching will be performed. Despite several trials and meta-analysis, the treatment of proximal humerus fractures are still much debated internationally and differs much per country and hospital. This observational study with a natural experiment design will create insight into which treatment modality is to be preferred for patients in whom there is disagreement about the optimal treatment strategy.

### Trial status

This is protocol version 2, dating from 28^th^ February 2020. Recruitment began 1^st^ of July 2020. Inclusion of patients is expected to be completed at July 2022. So far 102 patients from the Netherlands have been included, which are at the moment only conservatively treated patients. Switzerland has included 80 patients so far, which are exclusively operatively treated patients so far.
